**Figure 3 F3:**
[figure not shown]
**Simulated view of street scene as viewed through single-lens distance (panel A) and bifocal glasses (panel B)**. The footpath misalignment (a commonly reported environmental factor involved in outdoor falls) is clearly seen in panel A, but blurred in panel B.

The optometrist/counsellor will then instruct participants to use their new single-lens glasses for most walking and standing activities, and in particular when undertaking the following activities: walking up or down stairs outside the home, walking in the street and at shopping centres, walking or standing in other people's homes and unfamiliar buildings, negotiating rough or uneven ground and getting off and on public transport. Multifocal glasses use will not be discouraged for seated tasks, especially those that require frequent changes in focal length such as driving, and indoor standing and walking tasks that require changes in focal depth where there is minimal risk (e.g. cooking and selecting items in the supermarket).

To assist with the swapping of glasses, participants will be provided with a "glasses cord" for wearing around the neck and/or a hard or cloth glasses holder for keeping the second pair of glasses in a pocket. Intervention group participants will also be provided with a booklet reinforcing the advice. Table 1 outlines the strategies that will used to maximise compliance throughout the trial (Table 1). Any perceived barriers to compliance will be recorded.

**Table 1 T1:** Strategies to be used to maximise compliance

1	A strong evidence-based rationale for the intervention and clear recommendations will be provided.
2	The mechanism by which multifocal glasses can predispose to falls will be demonstrated during counselling using the example of the most commonly reported environmental factor involved in outdoor falls (Figure 2).

3	New glasses will be provided at no cost.

4	Perceived barriers to using two pairs of glasses will be identified and discussed during counselling.

5	An information brochure with recommendations and illustrations on appropriate use of glasses will be provided.

6	A hard/soft case glasses holder (to be worn around the neck and/or placed in the participant's pocket) to aid the swapping of glasses will be provided.

7	Second counselling sessions delivered over the phone or at home visits will address perceived barriers to use of glasses for participants with inadequate compliance, i.e. "never/occasionally" complying with the recommendations.

8	Written reminder cards will be provided with falls diaries and prompts will be made during follow-up telephone calls.

Participants in the control group will also have the same optometric examination as participants in the intervention group. For the estimated 80% of participants who will not need a change of prescription (n = 234), no new glasses will be prescribed. For the expected 20% who will require a prescription change (n = 56), updated multifocal lenses will be prescribed according to the above criteria and fitted at a second visit. Control group participants will be given no specific advice regarding the use of their glasses.

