**Methods/Design:**

Approximately 580 older people who are regular wearers of multifocal glasses people will be recruited. Participants will be randomly allocated to either an intervention group (provision of single lens glasses, with counselling and advice about appropriate use) or a control group (usual care). The primary outcome measure will be falls (measured with 13 monthly calendars). Secondary measures will be quality of life, falls efficacy, physical activity levels and adverse events.

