### Randomisation

After completion of the initial assessment, participants will be formally entered into the study and randomised to intervention or control groups. Participants will be stratified by assessment site (Greenwich or Prince of Wales Hospitals) and recruitment source (hospital or community contact).

Then each stratum will be randomly allocated in permuted blocks of 10 using sequentially-numbered opaque envelopes containing group assignment.

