**Figure 2 F2:**
[figure not shown]
**The distance contrast sensitivity tests**. Panel A shows a participant (with his chin placed on a comfortable chinrest to prevent head movement) viewing the test plate through the lower (reading) segments of his glasses. Panel B shows the participant looking directly at the test stimulus through the upper (distance) segments of his glasses. Any difference in contrast vision between the two conditions is then shown to the participant as part of the counselling session.

Participants will also be shown photographs of steps and streetscapes with and without simulated lower field blur to further reinforce why multifocal glasses may increase the risk of falls. Figure 3 shows the photographs of a simulated view of a street scene as viewed through single-lens distance (panel a) and bifocal glasses (panel b) (Figure 3). This counselling session will be conducted in line with the health belief model [20], and is considered crucial to convince older wearers of multifocal glasses that they are personally at risk of fall-related injuries and that the benefits of wearing single lens glasses outweighs the inconvenience of dealing with two pairs of glasses.

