### Outcomes

#### Primary outcome measure

The primary outcome measure will be the number of participant falls in the 13-month follow-up period following randomisation (this allows for an average time of one month for the provision of single-lens glasses following randomisation and 12-month further follow-up). Falls will be defined as 'inadvertently coming to rest on the ground or other lower level with or without loss of consciousness, and other than as a consequence of sudden onset of paralysis, epileptic seizure, excess alcohol intake or overwhelming external force' [21]. All participants will receive 13 calendars and questionnaires at the time of the baseline assessment. Participants will be asked to record falls (as well as information regarding any fall injuries and need for medical care) on the calendars and return them in pre-paid envelopes to the research centre each month. Participants who do not return calendars will be telephoned to ask for the information. Staff who receive falls calendars, make follow-up phone calls and enter data will be unaware of group allocation.

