### Compliance and adverse events

*Compliance *in the intervention group will be measured monthly by asking how often the participants complied with recommendations about wearing single-lens distance glasses when undertaking activities such as walking outdoors and descending steps etc. Reporting of the type of glasses worn during any fall will be recorded on the same questionnaire. Participants will be asked to return their compliance questionnaires in a separate pre-paid envelope to the falls calendar to the research centre each month. Staff who receive compliance questionnaires, make follow-up phone calls and enter data will be unaware of the occurrence of any participant falls. Any perceived barriers to compliance will be recorded at baseline and throughout the trial.

*Adverse effects *Falls occurring as a result of switching from single-lens to multifocal glasses or vice versa while undertaking an activity or any non-fall adverse outcome occurring as a result of the intervention will be recorded on the falls calendars.

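### Falls are self-reported by participants who know their arm, and Table 1 puts glasses-use reminders with the falls diaries, apparently in one arm only; keep the diary pack identical and name injurious falls as an outcome

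*Protocol article*

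**What the plan says.** The Primary outcome measure section defines the outcome: "The primary outcome measure will be the number of participant falls in the 13-month follow-up period following randomisation". Capture is by self-report: "Participants will be asked to record falls (as well as information regarding any fall injuries and need for medical care) on the calendars". On timing it states: "All participants will receive 13 calendars and questionnaires at the time of the baseline assessment". Staff who receive calendars, telephone participants and enter data are to be unaware of allocation, and participants who do not return a calendar are telephoned for the information.

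Under Randomisation: "After completion of the initial assessment, participants will be formally entered into the study and randomised to intervention or control groups". Under Intervention, the glasses are fitted at a second visit about four weeks after the initial assessment. Counselling is meant to "convince older wearers of multifocal glasses that they are personally at risk of fall-related injuries". Controls have the same optometric examination but no specific advice on using their glasses.

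Table 1 lists strategies to maximise compliance. Item 8 reads: "Written reminder cards will be provided with falls diaries and prompts will be made during follow-up telephone calls". The Compliance and adverse events section measures compliance monthly in the intervention group and says of the forms: "Participants will be asked to return their compliance questionnaires in a separate pre-paid envelope to the falls calendar to the research centre each month".

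The Secondary outcome measures section lists physical activity, falls efficacy and quality of life. The Statistical analysis section adds secondary analyses of falls within and beyond the home. Neither names fall injuries or medical care.

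**The concern.** The person who decides whether an event is written down knows the allocation and, in one arm, has been counselled that the new glasses reduce risk. That is inherent in the intervention. What is not inherent is placing a glasses-use reminder with the instrument that measures the primary outcome, when the other arm gets that instrument without it. A reminder could draw attention to the diary and raise recording. Belief in the glasses could lower the recording of minor falls. Either would change the recorded count in one arm for reasons other than falling. The article also names no fall outcome that depends less on a participant's readiness to record a trivial event, although the calendar collects the information for one.

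**Working it through.** **1. Is the card arm-specific?** Item 8 does not say so. It stands in a list of compliance strategies, compliance is measured in the intervention group, and controls have no recommendation to be reminded of. One-arm use is therefore an inference, but the only sensible one.

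**2. How would the card reach the participant?** All participants receive all 13 calendars at the baseline assessment. Randomisation follows completion of that assessment, and the glasses come about four weeks later. If the card is issued with the calendars, it must be added after allocation and would arrive before the glasses. If it is issued later, it is not provided with the diaries in the sense of the Primary outcome measure section. Same-day randomisation, or handing over the card at the fitting visit, would resolve this, but the article does not say which applies.

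**3. The plan's own target.** From the Sample size calculation section: 0.70 × 0.57 + 0.30 × 0.85 = 0.654 falls/person, and 0.654 / 0.85 = 0.769. This agrees with the stated IRR of 0.77.

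**4. Effect of differential recording.** Let r be the proportion of falls recorded in the intervention arm relative to control. Then observed IRR = true IRR × r. The article gives no value of r; those below are assumptions.

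| True IRR | r | Observed IRR | Comparison |
|---|---|---|---|
| 1.00 | 0.95 | 0.95 | 0.05 / 0.23 = 22% of the target reduction |
| 1.00 | 0.90 | 0.90 | 0.10 / 0.23 = 43% of the target reduction |
| 1.00 | 0.77 | 0.77 | the whole target reduction |
| 0.77 | 1.10 | 0.847 | benefit understated |

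**5. Effect on the test.** Evaluable per arm: 290 × 0.92 = 267. The standard error of the log IRR is √[(1/μ₁ + 1/μ₂ + 2k)/267], where μ₁ = 0.85 is the control mean, μ₂ the recorded intervention mean and k the negative binomial dispersion. The article does not state k, so a range is shown; the test is two-sided at 5%.

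- True IRR 1, r = 0.90, k = 0: μ₂ = 0.765, SE = √[(1.176 + 1.307)/267] = 0.0964, ln 0.90 = −0.105, ratio −1.09. The chance of a significant apparent benefit is Φ(−1.96 + 1.09) = 0.193.
- Same with k = 1.5: SE = 0.143, ratio −0.735, chance 0.110.
- With r = 0.95 the chance is 0.078 (k = 0) to 0.055 (k = 1.5). With r = 1 it is 0.025.
- True IRR 0.77, r = 1.10: power falls from 0.738 to 0.395 (k = 0), or from 0.504 to 0.245 (k = 1).

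The 0.738 at r = 1 is below the plan's 80%. That is a separate sample-size question, and nothing here depends on it.

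**The case against.** The strongest reply is that the article already protects outcome collection. Calendar staff are masked, missing calendars are chased by telephone in both arms, and compliance forms are returned separately to staff unaware of falls. The chase does limit differences in diary return. It does not reach a participant who returns a calendar without noting a minor fall. Reluctance to report after counselling would remain wherever the card is placed, and so would the monthly compliance questionnaire, itself an arm-specific cue.

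Several stronger readings are tempting and are not supported:

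- *The card is attached to each diary and acts as a monthly cue.* The text says only that cards are provided with the diaries.
- *Table 1 and the Primary outcome measure section contradict each other.* They leave the delivery unclear; neither rules out a workable arrangement.
- *The compliance questionnaire has its own outgoing mailing.* The separate pre-paid envelope is described for returning the form.
- *Injury and medical-care data will go unused.* The article names no outcome or analysis for them, but it does not say they will not be analysed, and the full protocol and analysis plan are not shown.
- *Those data are an objective check.* The same unmasked participants record them on the same calendar, and no verification against records is described.
- *The bias favours the intervention.* Plausible mechanisms run both ways.

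**Conclusion.** The point holds in limited form. Participants who know their arm record the primary outcome, and the outcome-collection material differs between arms if, as inferred, the cards go to the intervention arm alone. Existing safeguards address return and handling of diaries, not willingness to record a minor fall. Neither the sign nor the size of any bias can be established from the article. The figures show only that modest gaps would matter: under the assumed 10% under-reporting and k between 0 and 1.5, the chance of a false significant benefit rises from 2.5% to between 11% and 19%. The delivery of the cards needs clarifying. Injurious falls and falls needing medical care would add a less discretionary, though not independent, view of the effect.

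**What to change.** 1. Keep the falls diary pack identical in both arms. Give the reminder cards separately, for example with the glasses and booklet at the fitting visit or with the compliance questionnaire. Reconcile Table 1 item 8 with the Primary outcome measure section by stating when and how cards are issued. The monthly compliance questionnaire remains an arm-specific cue, and this should be acknowledged.

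2. Name injurious falls and falls needing medical care as secondary outcomes, compared by allocated group with negative binomial regression. Describe them as less discretionary than all falls but still self-reported and less precise. Report estimates with confidence intervals and weigh them alongside all falls. Do not adopt a rule that non-significance in them discounts the primary result, because with fewer events a true effect could fail such a test by chance.

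The cost is a change in how a card is handed over and two extra analyses of data already collected. The downside is that their intervals will be wide.

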### Outcomes

#### Primary outcome measure

The primary outcome measure will be the number of participant falls in the 13-month follow-up period following randomisation (this allows for an average time of one month for the provision of single-lens glasses following randomisation and 12-month further follow-up). Falls will be defined as 'inadvertently coming to rest on the ground or other lower level with or without loss of consciousness, and other than as a consequence of sudden onset of paralysis, epileptic seizure, excess alcohol intake or overwhelming external force' [21]. All participants will receive 13 calendars and questionnaires at the time of the baseline assessment. Participants will be asked to record falls (as well as information regarding any fall injuries and need for medical care) on the calendars and return them in pre-paid envelopes to the research centre each month. Participants who do not return calendars will be telephoned to ask for the information. Staff who receive falls calendars, make follow-up phone calls and enter data will be unaware of group allocation.

#### Secondary outcome measures

Secondary outcome measures will include physical activity levels, falls efficacy and quality of life assessed at baseline and 12 months. These measures are included to determine whether, as a result of fewer falls, the intervention has beneficial effects on an older person's abilities and quality of life. *Physical activity levels *will be assessed with the Adelaide Activities Profile, a validated scale which measures lifestyle activities using 21 items which generate four domains (domestic chores, household maintenance, service to others, and social activities) [14]. Physical and emotional wellbeing will be assessed using the *SF 12 Version 2 *composite physical and mental scores [15]. Falls efficacy will be assessed using the *FES-I *[16] in which level of concern about falling when carrying out 16 activities is rated on a 4-point scale.

### Compliance and adverse events

*Compliance *in the intervention group will be measured monthly by asking how often the participants complied with recommendations about wearing single-lens distance glasses when undertaking activities such as walking outdoors and descending steps etc. Reporting of the type of glasses worn during any fall will be recorded on the same questionnaire. Participants will be asked to return their compliance questionnaires in a separate pre-paid envelope to the falls calendar to the research centre each month. Staff who receive compliance questionnaires, make follow-up phone calls and enter data will be unaware of the occurrence of any participant falls. Any perceived barriers to compliance will be recorded at baseline and throughout the trial.

*Adverse effects *Falls occurring as a result of switching from single-lens to multifocal glasses or vice versa while undertaking an activity or any non-fall adverse outcome occurring as a result of the intervention will be recorded on the falls calendars.

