## Methods

### Participants

Participants will be recruited from the following sources: sampling of older people from the electoral roll in northern Sydney, residents of retirement (self-care apartment) villages in the Central Coast, Blue Mountains and Illawarra regions of New South Wales, outpatients and inpatients discharged from rehabilitation and orthopaedic wards at hospitals within northern and eastern Sydney, and responders to newspaper advertisements and media coverage.

Eligibility will be assessed primarily with a telephone screening questionnaire. Participants will be eligible for the trial if they are at a relatively high risk of falls defined as (a) aged 65–79 years with a Timed Up and Go Test (TUG) of 15+ seconds [10] and/or a history of one or more falls in the last 12 months or b) aged 80 years and over. Other inclusion criteria comprise: a user of bifocal, trifocal or progressive-lens glasses 3+ times/week when walking outdoors; having had a review by an optometrist or ophthalmologist in the last 12 months; not currently using single-lens distance glasses; and indicating that they are at least 'quite confident' of complying with the study recommendations.

People will be ineligible if they: reside in a high-care residential facility, have a cognitive impairment (a Mini-Mental State Examination (MMSE) [11] score of less than 24), a severe visual impairment (Melbourne Edge Test score of <16 dB) [12], insufficient English language skills to understand the assessment and/or intervention procedures, have planned ophthalmic surgery in the next 12 months, or have an unstable medical condition at enrolment.

The University of New South Wales Human Research Ethics Committee (HREC) approved the study protocol (HREC Number 04229) as have ethics committees at the participating hospitals. The participant flow diagram is presented as figure 1 (Figure 1).

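### Non-fall adverse outcomes are recorded only if caused by the intervention, so this part of the adverse-event measure has no control comparator, and the entries sit on the calendars meant to be handled blind

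*Protocol article*

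**What the plan says.** The protocol article describes adverse events in three places, and they do not line up.

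- **Abstract, Methods/Design:** "Secondary measures will be quality of life, falls efficacy, physical activity levels and adverse events".
- **Secondary outcome measures:** "Secondary outcome measures will include physical activity levels, falls efficacy and quality of life assessed at baseline and 12 months". Adverse events are not in this list.
- **Compliance and adverse events:** two kinds of event go on the falls calendars. The first is "Falls occurring as a result of switching from single-lens to multifocal glasses or vice versa while undertaking an activity". The second is described as "any non-fall adverse outcome occurring as a result of the intervention will be recorded on the falls calendars".

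The Statistical analysis section gives mixed models for the continuous secondary measures and states no comparison of adverse events between arms.

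The Primary outcome measure section gives calendars to all participants: "Participants will be asked to record falls (as well as information regarding any fall injuries and need for medical care) on the calendars". It adds that the staff who receive the calendars, telephone participants and enter the data will not know the allocation.

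**The concern.** For non-fall outcomes, causation by the intervention is a condition of being recorded. The usual order is to collect events in the same way in both arms, compare by allocation, and consider attribution afterwards. Reversing that order means the randomisation cannot be used to separate what the glasses cause from what would have happened anyway. Visual discomfort, difficulty adapting to a new prescription or a near miss while handling glasses can occur in either arm, and a number of controls also receive updated multifocals.

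Participants know whether they received a second pair of glasses, and the counselling aims to persuade them that the benefit outweighs the inconvenience. Attribution could be suppressed by that counselling or raised by the novelty of the glasses. Without a control rate, neither error can be seen.

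A second consequence concerns the primary outcome. The calendars are processed by staff who should not know the allocation. A written remark on them about the single-lens glasses can disclose it.

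**Working it through.** The protocol states no adverse-event rate or comparison, so there is no planned figure to reproduce. The check is a reading of the collection rules, followed by an illustration on assumed rates.

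**Step 1. Which events can each arm contribute?**

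| Event | Rule | Intervention | Control |
|---|---|---|---|
| Any fall, fall injury, need for medical care | Recorded whatever the cause (Primary outcome measure) | Yes | Yes |
| Fall while switching single-lens and multifocal glasses | Defined by switching, not by arm (Compliance and adverse events) | Yes | Possible, expected near zero |
| Non-fall adverse outcome | Must result from the intervention (Compliance and adverse events) | Yes | None possible |

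For the second row, the Participants section requires entrants to be "not currently using single-lens distance glasses". In the Intervention section, controls whose prescription is unchanged get nothing new ("For the estimated 80% of participants who will not need a change of prescription (n = 234), no new glasses will be prescribed"), and the rest get updated multifocals only. The criterion covers distance glasses only, so a control who owns single-lens reading glasses, or who obtains distance glasses later, could still record such a fall.

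For the third row, controls have neither the glasses nor the counselling ("Control group participants will be given no specific advice regarding the use of their glasses"), so no event of theirs can result from the intervention. Their count is zero by the rule itself. No later analysis can restore it, because the events are not collected.

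**Step 2. Adapting to new glasses.** The protocol expects 56 controls to be fitted with updated multifocals. Problems with new lenses are therefore plausible in both arms, but recordable as adverse outcomes in only one.

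**Step 3. Size, on assumed rates.** Let b be the true incidence of non-fall problems, equal in both arms, and a the share in the intervention arm that is attributed to the glasses. The expected recorded count is 290 × b × a in the intervention arm and 0 in the control arm. With b = 5% (an assumption):

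- a = 10%: 290 × 0.05 × 0.10 = 1.45
- a = 25%: 290 × 0.05 × 0.25 = 3.6
- a = 50%: 290 × 0.05 × 0.50 = 7.25

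At b = 20% and a = 50% the count would be 290 × 0.20 × 0.50 = 29.

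**Step 4. When would such a split look like a finding?** With 290 per arm and k events against 0, the two-sided Fisher p-value is 2 × C(290,k)/C(580,k). This gives 0.061 for k = 5, 0.030 for k = 6 and 0.015 for k = 7. Six attributed events, about 2% of the arm (6/290), would pass the 5% level with no true difference. With b = 5%, the binomial chance of six or more is about 0.4% at a = 10%, 16% at a = 25% and 73% at a = 50%.

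**Step 5. Blinding.** The protocol already has compliance questionnaires returned in a separate envelope from the calendars, and keeps the staff who handle those questionnaires unaware of falls. Putting intervention-attributed effects on the calendar works against that separation.

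**The case against.** The strongest reply is that the harm of most concern for this intervention, more falls or more injurious falls, is collected in both arms whatever the cause and is compared by intention to treat. **This stands.** A reader might infer that harm as a whole cannot be estimated as a randomised difference, or that a control who falls while changing glasses goes uncounted. Neither is right: that fall is in the primary outcome, and only its label as a switching fall may be missing.

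Second, the protocol plans no test of adverse events between arms. The secondary outcomes section leaves them out, and the rule stands beside intervention-arm compliance, where it can be read as descriptive monitoring. **This also stands**, and it limits the consequence: a spurious difference arises only if someone makes the comparison. It does not settle what the measure is, because the abstract lists adverse events alongside outcomes that are compared.

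Third, the article does not say who judges causation or how the item is worded, and such details may be in a fuller protocol. **This stands in part.** One cannot assert that participants alone make the judgement. The condition for recording is nevertheless stated, and it is one-sided whoever applies it.

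Finally, a reader might put the distortion at about 14 events against 0 (290 × 0.05 = 14.5). That requires every background event in the intervention arm to be blamed on the glasses, which nothing in the protocol supports.

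**Conclusion.** The point holds for non-fall adverse outcomes. As written, the rule gives this component of a named secondary measure no control comparator. For switching falls the control count is expected to be near zero but is not fixed at zero, so a claim that the whole adverse-event measure is zero in controls by construction would go too far.

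On an assumed 5% background incidence with 10% to 50% attribution, the distortion is about 1.5 to 7 recorded events against 0 among 290 per arm. The lower end would mislead nobody; the upper end could. No figure in the protocol changes.

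The primary analysis and sample size are unaffected by the missing comparator. The primary outcome is exposed only through the blinding risk, whose extent cannot be judged from the article because it depends on how often and how explicitly participants write about the glasses. This is an inexpensive improvement that should be made, not a flaw that undermines the trial.

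**What to change.** Preferred: ask both arms the same cause-neutral item in identical wording, covering any problem with glasses or vision and whether a fall happened while changing or removing glasses. Put it on a sheet separate from both the falls calendar and the compliance questionnaire, handled by neither blinded staff group. Answers about glasses could reveal allocation to the calendar staff, and answers about falls could reveal falls to the compliance staff. Report the results by allocation and treat attribution as a later step.

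Alternative: if only a description of the intervention arm is wanted, say so, and align the abstract, the Secondary outcome measures section and the Compliance and adverse events section. The entries should still come off the calendar, because relabelling alone leaves the blinding risk in place.

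Cost: one more form item for all participants, slightly more data entry, and someone outside the two blinded groups to handle the sheet.
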